Intubation is frequently required for patients in the intensive care unit (ICU) but is associated with high morbidity and mortality mainly in emergency procedures and in the presence of severe organ failures. Improving the intubation procedure is a major goal for all ICU physicians worldwide, and improving preoxygenation period may play a relevant role. However, until recently any device which can help physician to evaluate this period when pulse oxygen saturation is upper than 97% were available. Recently Oxygen Reserve Index (ORI) has been introduced by Masimo© as a surrogate of PaO2 in the range between 100 to 250mmHg. We propose to plan a study dedicated to improvement in SpO2 during intubation in ICU by adding ORI monitoring throughout the procedure.

# Justification of the study

## Positioning of the study

Endotracheal intubation (ETI) is a common procedure in ICUs (1). The risk factors in ICU patients result in a high complication rate (up to 50%) (2). Severe complications are severe hypoxaemia (25%), severe hypotension (25%), cardiac arrest (1-3%), and death (0.5-3%) (1,3,4). Risk factors for potentially fatal hypoxaemia are hypoxaemia before ETI and/or difficult ETI (5). Hypoxemia during ETI is associated with cardiac arrest occurrence (3,6) and morbidity.

Predicting hypoxaemia during ETI is challenging (5). Pre-oxygenation is universally recommended to reduce the risk by prolonging the safe apnoea time (7,8). Pulse oximetry saturation (SpO_2_) is monitored in ICU but only detects late-stage hypoxaemia. FeO_2_ is not available for assessing pre-oxygenation efficacy in the ICU. And this technique has limitations in the emergency setting (sensitivity to leaks) and is not available in ICUs (9). Moreover, in critically ill patients, particularly those with acute hypoxemic respiratory failure, FeO_2_ may not be a reliable measure of the effectiveness of preoxygenation: the reduction in functional lung volume leads, on the one hand, to a reduction in FRC (Fonctional Residual Capacity) and, on the other hand, to a shunt that reduces the efficiency of the alveolar-capillary interface (10). The result is that both SpO_2_ and FeO_2_ can be high while PaO_2_ is low. PaO_2_ can be considered the reference standard for evaluating the effectiveness of preoxygenation but unfortunately cannot currently be obtained at the bedside in real-time in clinical practice (9). Non-invasive ventilation (NIV) is currently recommended for patients with severe hypoxaemia but is associated with a higher risk of severe hypotension (11–15). Last, extended duration of preoxygenation did not help to increase quality of its own (16). Thus, at present, the effectiveness of pre-oxygenation cannot be evaluated in ICUs. Predicting the risk of hypoxaemia during ETI and optimising pre-oxygenation are two major therapeutic goals. A reliable tool for assessing the quality of pre-oxygenation is therefore needed.

The oxygen reserve index (ORI) is a new oxygenation-monitoring parameter measured continuously and non-invasively using a specific SpO_2_ sensor (Masimo Inc., Irvine, CA). ORI is a relative indicator of partial-pressure-of-oxygen (PaO_2)_ changes in the moderate hyperoxaemia range (17). ORI recording requires no additional intervention by clinicians in charge of the patient. The ORI is a dimensionless parameter that can range from 0.00 (PaO_2_<100mmHg) to 1.00 (PaO_2_>200mmHg). These were only prospective observational studies conducted on small numbers of patients in the context of planned surgery. Reported time intervals between the ORI decline below 0.4 and desaturation were 30 [20-60] seconds (18,19). We recently reported that, in non-hypoxaemic patients, the median time from an ORI fall below 0.4 and an SpO_2_ fall below 97% during apnoea was 81-s [Q1-Q3: 34-146], which is sufficient to allow preventive interventions. We recently observed than in non-hypoxemic patients, ORI decrease below 0.4 with a 81-s [34-146] median time before the SpO_2_ decrease below 97% during apnea which may allow preventive action. Interestingly, a higher ORI value during preoxygenation was independently protective against hypoxemia (20).

To help determine whether ORI monitoring can minimise hypoxaemia during ETI in critically ill patients, we designed a multicentre randomised controlled trial (RCT) to determine whether ORI monitoring is superior over standard care in preventing hypoxaemia.

## Benefits and risks for subjects taking part in the study

### Benefits

#### Individual benefit

If our hypothesis is verified, compared to usual care, use of ORI during preoxygenation will lead to increase in oxygenation parameters with higher safety for patient.

#### Collective benefit

The expected benefits of RCT for patients is better pre-oxygenation with less subsequent hypoxaemia when ETI is required in the ICU. ORI monitoring is expected to result in earlier recognition of impending hypoxaemia (when combined with other changes in the ETI procedure), thus improving the safety of ETI in the ICU. These benefits will be relevant to the very large number of ICU patients who undergo ETI worldwide.

### Risks

#### Individual risk

- Physical risks and constraints

Risks for patients included in the study are negligible. Previous studies on use of ORI during intubation in intensive care unit showed a good tolerance profile (20).

- Disease-related risks

Patients eligible for study inclusion will have a critical illness associated with a high risk of complications including nosocomial infections, organ failure, metabolic disorders, and subsequent death. Care given to the study patients will be appropriate for their health condition, as used routinely in the participating ICUs and as decided by the bedside physicians and ICU teams. Thus, this research will not increase disease-related risks.

#### Collective risk

The NESOI-2 study is not associated with any collective risk. This study will not generate additional costs for the participating centres.

### Benefit / risk balance

Given the characteristics of the research project, the chief investigator considers that this research has minimal risks and constraints, based on the following arguments:

- Current practice for peri-intubation procedures in intensive care unit are heterogeneous (21);
- Few adverse event occurred during observational study dedicated to evaluation of ORI monitoring (20);
- ORI monitoring has a CE marking approval;

In conclusion, given the potential benefits previously stated in point 1.2.1 and the minimal risks and constraints associated with the research, the risk/benefit ratio is extremely favourable.

## Statement that the research project will be conducted in compliance with the study protocol and with good clinical practice guidelines

The investigator undertakes to ensure that this research is conducted:

- - In compliance with the study protocol, and
  - In compliance with current French and international good clinical practice guidelines.

**The bibliographical references are appended to the document.**

# Objectives and endpoints

## Primary objective and endpoint

### Primary objective

The primary objective is to determine whether ORI monitoring increases the lowest oxygen saturation level during the interval between the first laryngoscopy (defined as introduction of the laryngoscope into the mouth) and the end of the second minute after successful ETI.

### Primary endpoint

Lowest oxygen saturation, measured by Masimo Rad7 oximeter, during the interval between the first laryngoscopy (defined as introduction of the laryngoscope into the mouth) and the end of the second minute after successful ETI (22).

## Secondary objectives and endpoints

### Secondary objective(s)

- To determine whether ORI monitoring increases the lowest oxygen saturation level according to local oximeter.

- To determine whether ORI monitoring increases the lowest oxygen saturation level according to subgroups.

- To assess safety of ORI monitoring.

- To assess efficacy of ORI monitoring.

### Secondary endpoint(s)

- Sensitivity analysis of primary endpoint
  - Lowest oxygen saturation, measured by local oximeter, during the interval between the first laryngoscopy (defined as introduction of the laryngoscope into the mouth) and the end of the second minute after successful ETI.
- Sub-group analysis of primary endpoint
  - Lowest oxygen saturation in pre-defined subgroups
    - Body mass index (<30 or ≥30)
    - Reason for ETI: hypoxaemia/other
    - Shock/No shock at inclusion
    - Difficult intubation (yes or no)
    - ORI threshold (<0.6 or ≥0.6)

- Safety outcome

- - Occurrence of at least one severe life-threatening complication: death, cardiac arrest, arterial systolic pressure <90 mmHg, and/or SpO_2_<80% and occurrence of each one.

- Efficacy outcome

- - ICU mortality
  - 28-day mortality
  - ICU and hospital stay length
  - Mean cognitive score at day 28 between two groups (modified Telephone Interview for Cognitive Status (F-TICS-m) (23)

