# Study design AND CONDUCT

## Study schedule

Consecutive ICU patients requiring ETI will be randomly allocated to ETI with or without ORI monitoring before beginning of preoxygenation, with stratification by centre, expert or nonexpert intubator status (experts: ≥5 years’ ICU experience, or ≥1 year ICU experience plus ≥2 years’ anaesthesiology training) (24), and NIV or others devices for preoxygenation. Two intubators including at least one expert will be present throughout ETI. At least one of the intubators will be trained in ORI monitoring, i.e., will have attended an education session and used the device twice.

Randomisation will be via an electronic case-report form, using a balanced scheme with stratification as described above.

Informed consent will be obtained from the patient or next of kin.

Patients for whom no family member is available to receive information and consent to participate in the study within a time frame compatible with the study design will be included in the study after completion of an emergency consent form by the patient's attending physician. Informed consent will be sought from the patient upon regaining decision-making capacity.

Data collected:

- Patient characteristics: demographics, Simplified Acute Physiologic Score II, activity level (Knaus), Charlson comorbidity index, ICU admission diagnosis, reason for ETI, Sequential Organ Failure Assessment [SOFA] score, vital signs at enrolment, criteria for difficult face-mask ventilation, criteria for difficult intubation, and MACOCHA score
- Before, during ETI, and 2 minutes after successful ETI: ORI, Mallampati score, pre-oxygenation methods and duration, type and dosage of sedatives and neuromuscular blockers, Cormack-Lehane grade, glottic opening score, number of ETI attempts before success (each introduction of the laryngoscope into the mouth is a separate laryngoscopy attempt), with details: manoeuvres during laryngoscopy, reason for ETI failure, difficult ETI , duration of ETI , need for face-mask ventilation after first ETI attempt, need for gum elastic bougie, and types of life-threatening and other complications. Pulse oximetry will be recorded throughout the ETI procedure.
- Day 1 to 7: SOFA score
- Day 28: Mortality, ICU stay length, hospital stay length, cognitive score (F-TICS-m)

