**Analysis of primary endpoint according to subgroup**

Primary endpoint will be analyzed according to pre-defined subgroups variables:

- - - Body mass index (<30 or ≥30)
    - Reason for ETI: hypoxaemia/other
    - Shock/No shock at inclusion
    - Difficult intubation (yes or no)
    - ORI threshold (<0.6 or ≥0.6)

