**Analysis of secondary endpoints**

All analyses will be adjusted on stratification criterion.

- Occurrence of at least one severe life-threatening complication: death, cardiac arrest, arterial systolic pressure <90 mmHg, and/or SpO_2_<80% and occurrence of each one using logistic mixed-effect regression model.

- The rates of death in ICU and at 28 days will be calculated via Kaplan-Meier plots and compared between groups using Cox regression models.

- ICU and hospital length of stay will be compared using Fine and Gray model to take into account death as competing risk.

- Cognitive score evaluated by F-TICS-m will be compared between groups using linear mixed effect regression model. Patients dead at day 28 will be not included on this analysis.

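### The safety outcome counts systolic pressure below 90 mmHg with no time window and no reference to pressure before randomisation, so hypotension already present can count in both arms and dilute a true difference

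*Protocol*

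**What the plan says.** Section 2.2 (Secondary endpoints) gives one safety outcome, a composite of severe complications: death, cardiac arrest, "arterial systolic pressure <90 mmHg, and/or SpO_2_<80% and occurrence of each one". Section 7.2 and the protocol summary repeat the same bare pressure threshold. None of these places states a time window, a new-onset condition, or how a patient already below 90 mmHg is handled. The primary endpoint, by contrast, has an exact window, from first laryngoscopy to two minutes after successful intubation.

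Four other places bear on the point:

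- Sections 4.2 and 4.3 set no blood-pressure limit and do not exclude shock. The subgroup list includes "Shock/No shock at inclusion", so such patients are expected.
- Section 5.1 collects "types of life-threatening and other complications" in a list headed "Before, during ETI, and 2 minutes after successful ETI". It also collects "vital signs at enrolment".
- Section 7.2 analyses the composite "and occurrence of each one using logistic mixed-effect regression model", adjusted on the stratification criteria: centre, intubator status and preoxygenation device.
- Section 1.1 quotes severe hypotension at 25% and says that non-invasive ventilation for preoxygenation is "associated with a higher risk of severe hypotension".

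**The concern.** A fixed threshold without a baseline reference measures two things together: hypotension that arises during the procedure, which the intervention might change, and hypotension present beforehand, which it cannot. Randomisation spreads the second kind evenly over the arms. It therefore creates no false difference, but it raises the event rate in both arms and pulls the odds ratio towards 1.

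In an efficacy analysis such dilution is conservative. In a safety analysis it lowers the chance of seeing a harm that exists. Hypotension is the harm the protocol itself links to one of the preoxygenation methods, and by its own figures it is one of the two commonest severe complications. The model contains neither enrolment pressure nor shock status, so nothing in the stated analysis recovers the lost contrast.

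**Working it through.** **The plan's own figure.** The protocol gives no power or expected rate for the safety outcome. Its only power figure, 85% for the primary endpoint, can be reproduced. With 475 per arm, SD 10 and a 2-point difference, power is 86.9%; with the difference reduced by 5% for cross-over (1.9 points) it is 83.4%. That figure does not bear on this point.

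**Inputs.**

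- 950 patients at 1:1, so 475 per arm (section 7.2).
- Control risk of new hypotension: 25%, the background rate in section 1.1 used as a proxy.
- Risk with ORI monitoring: 32%, assumed; 34% as a second case.
- b, the share already below 90 mmHg before randomisation: not in the protocol, varied from 0 to 30%.

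**Formula.** If existing hypotension counts, the observed risk in an arm is b + (1 − b) × (new-onset risk). The observed difference is therefore (1 − b) × (new-onset difference), whatever harm is assumed. The same holds for the composite: every patient already below 90 mmHg is an event, so the composite risk is b + (1 − b) × (composite risk in the others).

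Power uses the normal approximation for two proportions, two-sided 5%: Φ[(d − 1.96·s0)/s1], with s0 from the pooled proportion and s1 from the separate proportions.

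**One row in full, b = 15%.** Controls: 0.15 + 0.85 × 0.25 = 36.25%. ORI: 0.15 + 0.85 × 0.32 = 42.2%. Difference 5.95 points. s0 = √(0.39225 × 0.60775 × 2/475) = 0.03168. s1 = √[(0.3625 × 0.6375 + 0.422 × 0.578)/475] = 0.03162. Power = Φ[(0.0595 − 0.0621)/0.03162] = Φ(−0.082) = 47%.

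**Results for 25% versus 32%.** The last column analyses only patients at or above 90 mmHg at enrolment, 475 × (1 − b) per arm.

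| b | Observed risks | Odds ratio | Power, existing cases counted | Power, patients at risk only |
|---|---|---|---|---|
| 0 | 25.0% v 32.0% | 1.41 | 67% | 67% |
| 5% | 28.8% v 35.4% | 1.36 | 59% | 64% |
| 10% | 32.5% v 38.8% | 1.32 | 53% | 62% |
| 15% | 36.3% v 42.2% | 1.28 | 47% | 60% |
| 25% | 43.8% v 49.0% | 1.24 | 37% | 54% |

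**Second case, 25% versus 34%.** Power with existing cases counted, against patients at risk only: 80% v 84% at b = 5%, 74% v 82% at 10%, 61% v 78% at 20%, 49% v 72% at 30%.

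**No true effect.** Both arms then have the same observed risk for any b, so type I error does not change.

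**The case against.** **The text is silent rather than wrong.** No sentence says that existing hypotension counts. A complication that occurs is naturally read as arising from the procedure, and section 1.1 uses the word that way. The heading in section 5.1 that begins before intubation covers a mixed list (airway scores, drugs, laryngoscopic view, complications), so it need not mean that complications are counted from before the procedure. A statistical analysis plan that is not shown may settle the matter. This stands as a limit: the literal rule can count existing hypotension, but it is not shown that it will. The endpoint wording is nevertheless fixed in the protocol, and staff filling the case report form in real time need one definition.

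**The size is assumed.** Neither b nor any effect of ORI monitoring on blood pressure is in the protocol. Shock treated with vasopressors need not mean a pressure below 90 mmHg. The 25% may itself include existing cases, in which case adding b counts some of them twice. This also stands; at b = 5% the loss is small.

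**The components are analysed separately.** A reader might infer that the composite can hide a rise in hypotension behind a fall in desaturation. For example, if SpO2 below 80% fell from 25% to 18% while hypotension rose from 25% to 32% (independence assumed), the composite would be 1 − 0.75 × 0.75 = 43.8% against 1 − 0.82 × 0.68 = 44.2%. The arithmetic is right, but the inference is not supported: the plan compares each component between arms, and the hypotension comparison would show 25% against 32%.

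**Conclusion.** The point holds as a weakness of definition. As worded, the pressure component can include hypotension that preceded randomisation. If it does, the absolute difference shrinks by (1 − b) in that component and in the composite. The cost runs from slight (about 5 points of power at b = 5%) to substantial (about 17 points at b = 25%), given 25% versus an assumed 32% and assumed values of b.

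Two stronger readings go beyond the protocol. One is that existing hypotension hides a real increase: no figure in the protocol shows an increase, and the effect is attenuation of unknown size. The other is that the analysis is biased towards declaring ORI monitoring safe: randomisation balances existing hypotension, type I error is intact, and no stated rule infers safety from a non-significant result. This is a secondary outcome. The change is worth making because it costs almost nothing.

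**What to change.** In sections 2.2 and 7.2:

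1. State the window for the safety outcome: from randomisation (start of preoxygenation) to two minutes after successful intubation.
2. Define the pressure event as new: systolic pressure below 90 mmHg in that window, in a patient at or above 90 mmHg at enrolment, measured before randomisation.
3. Do not use the last reading before induction as the reference. It is taken after randomisation and after ORI-guided preoxygenation has begun. It would select patients on a variable the intervention may affect, and would drop hypotension that arises during preoxygenation.
4. Report patients already below 90 mmHg at enrolment separately. They stay in the composite for its other components.
5. Adjust the hypotension and composite models for enrolment systolic pressure or shock status.
6. Keep the planned analysis of each component. A further composite without SpO2 below 80% is optional.

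The cost is wording and a little analysis. Vital signs at enrolment are already collected, and shock at inclusion is needed for the planned subgroup; check only that the case report form records systolic pressure before randomisation. Two small drawbacks: patients hypotensive at enrolment cannot contribute a hypotension event, and comparability with earlier composites is slightly reduced.

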# Study treatments and products

## Description of the product(s) and mode of administration

### Experimental product(s)

The oxygen reserve index (ORI) is a new oxygenation monitoring parameter measured continuously and noninvasively. It can be obtained from specific SpO2 sensor manufactured by Masimo (Masimo Inc., Irvine, CA). It is a relative indicator of partial pressure of oxygen (PaO_2)_ changes in the moderate hyperoxemia range. It did not require additional intervention from doctor or nurse in charge of the patient. The ORI is a dimensionless parameter that can range from 0.00 (PaO2<100mmHg) to 1.00 (PaO2>200mmHg). It is measured by a multi-wavelength pulse co-oximeter placed on the tip of a finger (Rainbow SET, Masimo Inc., Irvine, CA) (17). The device analyzes variations in the pulsatile blood absorption of incident light at both the arterial and venous levels. It is a relative indicator of PaO_2_ changes in the moderate hyperoxemia range. When pure oxygen is administered, SaO_2_ reaches 100% when PaO_2_ reaches 100 mmHg. Beyond that, PaO_2_ continues to increase and both SaO_2_ and SpO_2_ remain at 100%, whereas the ORI increases non-linearly from 0.00 (PaO_2_~100 mm Hg) to 1.00 (PaO_2_~200 mmHg). Dedicated sensors will be provided by Masimo for study purpose.

## Authorised and unauthorised treatments in the context of the protocol

### Authorised treatments

All medications whose use in standard practice in ICU patients will be authorised for use according to the specific needs of each patient.

### Unauthorised treatments

No treatment used according to its marketing authorisation in contra-indicated in this trial.

# Study population

## Description of the population

The trial population will be adults (18 years of age or older) who need endotracheal intubation while hospitalized in ICU. Patients will be eligible for enrolment if they meet all the following inclusion criteria and none of the non-inclusion criteria.

Patients participating in intubation research with an oxygenation endpoint will not be eligible for inclusion in the NESOI-2 protocol.

## Inclusion criteria

- ICU admission and need for ETI to allow mechanical ventilation
- Need for supplemental oxygen (via any device and at any flow rate) to obtain SpO_2_>97%
- Patient or next of kin informed about the study and having consented to participation of the patient in the study (patients with coma are unable to consent). If patient is no competent and no next of kin can be contacted during screening for the study, trial inclusion will be completed as an emergency procedure by the ICU physician, in compliance with French law
- Patients affiliated to a social security system

## Non-inclusion criteria

- Fiberoptic intubation required according to physician in charge
- Contra-indications to laryngoscopy (e.g., unstable spinal lesion)
- Insufficient time to include and randomise the patient (e.g., because of cardiac arrest)
- Age <18 years
- Currently pregnant or breastfeeding
- Correctional facility inmate
- Under guardianship, curatorship or under protection of justice

